### 2.4. Vulnerable Populations

Although vulnerable subjects will not specifically be recruited for this study, vulnerable subjects may be present in the potential subject pool. Vulnerable subjects are defined as patients who are pregnant, fetuses/children, or prisoners. Additional procedures will not be required to ensure protection for these human subjects.

### 2.5. Standard of Care

The trial design calls for both groups to receive the standard-of-care treatment. The recognized standard of care (SOC) for diabetic foot ulcers (DFUs) is debridement, off-loading, maintaining proper moisture balance, and control of bacterial burden [13]. Reducing bacterial load and moisture balance are addressed in the protocol. The gold standard for off-loading the diabetic foot is a total contact cast (TCC) [14]; however, few clinical trials have utilized this method for a variety of reasons, including expense, difficulty in application, and patient acceptance. In antiseptic trials that require daily applications of the study agent TCCs are impractical. The alternative is the use of a fixed ankle walker; however, patient adherence has been a problem with removable walkers [15]. Recent advances in off-loading boots may improve patient adherence. Debridement is an essential procedure in the treatment of the DFU [16]. It is advisable to monitor the extent of debridement in DFU clinical trials. In this trial, debridement will be assessed through weekly digital monitoring of pre- and post-debridement photos.

The mainstay of the standard of care for VLUs is multilayer compression and routine debridement [1]. The authors recommend supplying the same compression device to all of the sites to standardize the compression. Small differences in compression devices can add heterogeneity to the trial.

### 2.6. Subject Characteristics

Patients who suffer from acute or chronic wounds will be recruited for this study from participating wound clinics. Once patients agree to adhere to the study schedule (weekly visits and follow-up regimen) and read and sign the IRB approved Informed Consent Form, screening will be conducted to determine whether the inclusion criteria were met:The patient must be at least 18 years old, and if female of childbearing potential, must be willing to use acceptable methods of contraception (birth control pills, barriers, or abstinence);The presence of a DFU extending through the dermis or subcutaneous tissue or the presence of a full-thickness VLU;To assess the primary endpoint of the trial, the index ulcer must have been present for longer than four weeks prior to screening;A DFU size between 0.75 cm^2^ and 5 cm^2^ and a VLU size between 2.0 cm^2^ and 20.0 cm^2^ at first treatment visit;Circulation to the affected extremity is adequate, as demonstrated by a transcutaneous oxygen measurement (TCOM) or skin perfusion pressure (SPP) measurement of ≥30 mmHg, OR an ankle brachial index between 0.7 and ≤1.3 OR a toe brachial index > 0.5 within 3 months of the first screening visit.

If any of the following exclusion criteria are met, patients will be excluded from participating in the study:Study ulcer(s) deemed by the investigator to be caused by a medical condition other than diabetes;Surgery for operative debridement or revascularization is planned for the ulcer to be treated;Index ulcer has a history of cancer or, in the opinion of the investigator, is suspected to be cancer and should undergo an ulcer biopsy to rule out a carcinoma of the ulcer;Subjects with a history of more than two weeks of treatment with immunosuppressants (including systemic corticosteroids of > 10 mg daily dose), cytotoxic chemotherapy, or application of topical steroids to the ulcer surface within one month prior to first screening visit, or who receive such medications during the screening period, or who are anticipated to require such medications during the study;History of radiation at the ulcer site;Subject who cannot adhere to strict offloading according to protocol standards, in the opinion of the investigator;Presence of any condition(s) that seriously compromise(s) the subject’s ability to complete this study or has a known history of poor adherence with medical treatment;Active treatment of infection anywhere in the body with IV antibiotics at screening and baseline;Suspected or confirmed signs/symptoms of gangrene on any part of the affected limb;Known osteomyelitis or bone infection of the affected foot or leg, as verified by diagnostic imaging within 30 days prior to enrollment;Subject is pregnant or breastfeeding;Study ulcer has a history of treatment with hyperbaric oxygen, growth factors or other biologic treatments, or a cellular or tissue-based product (CTP) within 30 days of enrollment;Subject has a known or suspected allergy to products under study;Concurrent disease or drugs known to induce severe photosensitivity of the skin, such as porphyria.

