## 2. Materials and Methods

BLEU is a randomized double-blind controlled clinical trial comparing a synergistic antimicrobial cleanser (AMC) and an antimicrobial gel (AMG) to a normal saline wash and an amorphous gel (NSS-HG) in reducing bioburden and promoting healing in chronic lower extremity ulcers (clinicaltrials.gov #NCT05107050). This study will be conducted at up to five SerenaGroup^®^ Research Foundation centers throughout the United States with up to 60 subjects with acute or chronic non healing wounds participating. The study is anticipated to be completed within one year. The study population will be drawn from patients suffering from chronic wounds who are attending wound clinics or residing in skilled nursing facilities. Section 2.6 details the inclusion and exclusion criteria for the BLEU trial.

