### 2.7. Study Procedures

At the screening visit (SV), Day 0, patients will be provided with an informed consent procedure and documentation of the informed consent discussion. The IRB-approved informed consent is obtained prior to performing any trial-related procedures. Once consent is obtained, the physician will document the onset of the ulcer per medical record or patient report, with preference to documentation over self-reporting. The patient’s medical history and demographic information will be recorded. For female patients of childbearing potential, urine or blood pregnancy tests will be conducted. A physical examination will follow and is focused on the integumentary system. Next, a Fitzpatrick score will be assigned. The Fitzpatrick score is a validated assessment of skin tones meant to increase enrollment of minority populations in clinical trials. This is necessary, as an objective assessment of skin color is recommended in all clinical trials, and when using optical diagnostics, the color of the skin is important data.

Due to the inaccuracy of length times width measurements using a hand-held ruler, wound surface area measurement will be assessed using digital planimetry. There are several systems commercially available that accurately measure wound surface area. In this trial, the MolecuLight device in standard photographic mode will provide accurate planimetry. Finally, the patient will complete a baseline pain assessment using a visual analog or numeric scale. Prior or concomitant medications will be reviewed. Quality of life questionnaires will not be used in this trial design due to the short duration of the trial.

This trial design does not incorporate a run-in period such as those used for advanced wound care modalities (e.g., cellular and tissue-based products for wound care (CTP). The goal of antiseptic trials is to identify products that reduce the level of bacteria in the wound; therefore, a run-in to assess healing rate prior to enrollment is unnecessary.

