### 2.8. Statistical Methods

Summary statistics including mean, median, interquartile range, counts, and percentages are used to summarize demographic and treatment data collected from patients.

When determining sample size, a power of 80% is needed to detect a difference between groups of 0.35. With sample sizes of 30 patients per group, 80% power is achieved.

A chi-square test of independence will be conducted to assess endpoints concerning proportions. For the BLEU trial, the chi-square test will be used to assess the primary and secondary endpoint. The primary endpoint is to determine the relationship between the treatment and the patient, reaching a threshold of 40% PAR in four weeks. The secondary endpoint is to determine the relationship between the treatment and a reduction of bacterial load of <10^4^ CFU/g (by Fluorescence) by the fifth treatment visit. The assumptions of the chi-square test of independence must be met. These include randomly selected patients, independent treatment groups, and the use of two categorical frequency variables. The expected frequency for each group must be greater than five. A significance level of 0.05 will be used for this hypothesis test. For the primary endpoint, the null hypothesis states that the proportion is equal for both treatments, whereas the alternative hypothesis states that the proportion is not equal for both treatments. Statistical software such as R (version 4.3.1), Excel (version 365), or a TI-83 calculator (TI-83 Plus Graphing Calculator|Texas Instruments) will be used to calculate the chi-square test statistic and the *p*-value.

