A *t*-test will be used to evaluate endpoints concerning mean differences between treatment groups. For the BLEU trial, the t-test will be used to assess the secondary endpoint. The secondary endpoint is to determine the percentage wound area reduction at four weeks. The assumptions of the t-test must be met. These include randomly selected, independent, normal variables that have similar variance. A significance level of 0.05 will be used for this hypothesis test. For these endpoints, the null hypothesis states that the mean difference between the baseline and the end of the study is equal for both treatments, whereas the alternative hypothesis states that the mean between the baseline and the end of the study is not equal for both treatments. Statistical software such as R (version 4.3.1), Excel (version 365), or a TI-83 calculator (TI-83 Plus Graphing Calculator|Texas Instruments) will be used to calculate the test statistics and the *p*-value.

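### Ulcer duration is recorded at screening but used in neither stated PAR test; adjusting for it would be a cheap, modest gain in precision, mainly for the secondary mean-PAR comparison

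*Protocol article*

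**What the plan says.** Section 2.6 gives a minimum ulcer duration: "the index ulcer must have been present for longer than four weeks prior to screening". The criterion is introduced as serving the primary endpoint. No inclusion or exclusion criterion gives a maximum, so an ulcer of five weeks and one of several years can both enter.

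Duration will be available for everyone. At screening, Section 2.7 says, "the physician will document the onset of the ulcer per medical record or patient report", with documentation preferred to self-report, and Table 1 lists this as a Day 0 item. The same section stratifies randomization by site and by nothing else.

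Section 2.8 then names the tests. "A chi-square test of independence will be conducted to assess endpoints concerning proportions", and this covers the primary endpoint, reaching 40% PAR in four weeks. For mean percentage area reduction at four weeks, "the t-test will be used to assess the secondary endpoint". Apart from the baseline area that PAR itself contains, no baseline variable enters either test.

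The trial is small: Section 2 plans it "with up to 60 subjects with acute or chronic non healing wounds participating", and Section 2.8 states "With sample sizes of 30 patients per group, 80% power is achieved".

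**The concern.** If older ulcers shrink more slowly over four weeks, duration explains part of the spread in PAR. A test that leaves it out keeps that spread in its error term, so the interval for the treatment difference is wider than it need be. With 30 per arm, one arm can also draw noticeably more long-standing ulcers by chance. Site-stratified blocks do nothing to prevent this, and the stated tests cannot take it into account.

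At stake is some power and the reading of the result if such an imbalance appears. An adjustment chosen after the imbalance has been seen would look data-driven; one fixed beforehand would not.

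**Working it through.** **Inputs from the documents.** 30 per group, 1:1 allocation, two-sided 0.05, 80% power (Sections 2.7 and 2.8). The power statement is "a power of 80% is needed to detect a difference between groups of 0.35". I read 0.35 as a difference in proportions, because the primary test is a chi-square test. The control responder rate is not stated, so it is varied.

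**Assumed inputs.** The correlation r between (log) duration and PAR, and the odds ratio per SD of duration for reaching 40% PAR. The documents give neither.

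**Step 1: the plan's own figure.** For two proportions with pooled variance under the null and no continuity correction,

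power = Φ{[0.35·√30 − 1.96·√(2·p̄(1−p̄))] / √[p1(1−p1)+p2(1−p2)]}.

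- 0.20 vs 0.55: (1.917 − 1.342)/0.638 = 0.90, power 81.6%
- 0.25 vs 0.60: 79.9%
- 0.325 vs 0.675 (the least favourable pair): 78.9%

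The required size is at most 31 per arm. The stated 80% with 30 per group is reproduced.

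**Step 2: mean PAR.** Adjustment multiplies the residual variance by 1 − r². The equivalent gain in subjects is 1/(1 − r²) − 1. Starting from 80% power, the new power is about Φ(2.80/√(1 − r²) − 1.96).

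| Assumed r | Variance removed (r²) | Equivalent extra subjects | Unadjusted N matching 60 adjusted | Power |
|---|---|---|---|---|
| 0.1 | 1% | 1.0% | 60.6 | 80.4% |
| 0.2 | 4% | 4.2% | 62.5 | 81.6% |
| 0.3 | 9% | 9.9% | 65.9 | 83.6% |
| 0.4 | 16% | 19.0% | 71.4 | 86.4% |
| 0.5 | 25% | 33.3% | 80.0 | 89.9% |

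This ignores the lost degrees of freedom. At r = 0.1 that loss could cancel the gain.

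**Step 3: the 40% PAR responder endpoint.** Simulation with 30 per arm and 3,000 trials per scenario compared the unadjusted chi-square test with a linear regression of response on arm and standardised duration. Site was not modelled.

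| Odds ratio per SD | 0.20 vs 0.55: unadjusted → adjusted | 0.325 vs 0.675: unadjusted → adjusted |
|---|---|---|
| 1.5 | 82.4 → 83.6% | 80.1 → 80.3% |
| 2 | 80.8 → 84.2% | 80.7 → 83.7% |
| 3 | 82.1 → 88.0% | 79.3 → 85.3% |

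With no treatment effect (responder rate 0.40 in both arms), the unadjusted test rejected in 4.3 to 5.1% of trials, so its type I error is held.

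**Step 4: chance imbalance.** The standard error of a standardised baseline difference is √(2/30) = 0.258. The chance of an absolute difference above 0.25 SD is 33%, and above 0.5 SD it is 5%. The simulated trials with more than 0.25 SD against the active arm made up 15 to 17% of all trials. Their power was:

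| Odds ratio per SD | 0.20 vs 0.55: unadjusted / adjusted | 0.325 vs 0.675: unadjusted / adjusted |
|---|---|---|
| 1.5 | 77% / 83% | 71% / 77% |
| 2 | 69% / 84% | 64% / 82% |
| 3 | 60% / 86% | 56% / 83% |

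These figures are conditional on an unfavourable imbalance. The favourable direction is equally likely.

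**The case against.** The strongest reply is that nothing here is an error. Unadjusted tests in a randomized trial are valid, and chance imbalance is part of the sampling error they already allow for. This stands. A reader might infer that the planned tests are biased or the trial underpowered; the reproduced power and the simulated type I error show neither.

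Second, the documents do not show that duration predicts PAR among ulcers already past four weeks. The wording of the inclusion criterion justifies an entry threshold, not a gradient above it. This also stands, and is why the size is shown as a range that includes a negligible case.

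Third, the larger gains belong to the t-test, which Section 2.8 makes secondary. A reader might carry the 33% over to the primary endpoint. Step 3 does not support that.

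Fourth, adjusted analyses are often left to an analysis plan, which is not shown. This carries weight for a supportive analysis of the responder endpoint. It carries less for mean PAR, where the article names the t-test in committed terms along with its hypotheses and significance level. Replacing that test changes a stated method.

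Fifth, duration is not the only candidate covariate. Ulcer type and baseline area differ by design (0.75 to 5 cm² for diabetic foot ulcers, 2 to 20 cm² for venous leg ulcers), and the documents do not rank duration above them. Onset may also rest on patient report, and recall error would weaken any association. Both remarks are fair. They limit the expected gain but do not remove the case for using a value already collected.

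**Conclusion.** The point holds as a modest, optional improvement in precision. It corrects no error: both tests are valid and the sample size is sound on its stated terms.

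For mean PAR, adjustment is worth between about 1% (r = 0.1) and 33% (r = 0.5) more subjects. For the responder endpoint the gain is about 0 to 3 power points at odds ratios of 1.5 to 2 per SD, and about 6 points only at 3. Protection against an unfavourable draw is larger, but applies to roughly one trial in six.

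All of this rests on an assumed association between duration and healing, a roughly linear effect of log duration, and reasonably accurate onset dates. The absence of a maximum duration or a run-in is not itself a fault on this evidence. Section 2.7 gives a reason for having no run-in, and the point does not call for a change to who may enter.

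**What to change.** In Section 2.8, replace the t-test for 4-week PAR with a prespecified ANCOVA containing treatment, log ulcer duration and site. Site belongs in the model because it is the stratification factor.

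Keep the chi-square test as the primary test of the 40% PAR endpoint. Add a covariate-adjusted marginal risk difference, with its interval, as a supportive analysis. Leave the eligibility criteria as they are, and fix the wording before unblinding.

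The cost is a change of text and a few degrees of freedom: one for duration and, with up to five centers, at most four for site. With 60 subjects this takes the error degrees of freedom from 60 − 2 = 58 to no fewer than 58 − 5 = 53. Patient-reported onset will add some noise to the covariate. No new data, visits or subjects are needed. The model does need statistical software; the calculator that Section 2.8 allows for the t-test would not be a practical tool for it.

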### 2.1. Objectives and Endpoints

The primary objective for the BLEU clinical trial is to compare healing rates (percent area reduction, PAR) between normal saline wash and an amorphous gel (NSS-HG) to the combination of a synergistic antimicrobial cleanser (AMC) and an antimicrobial gel (AMG) in chronic lower extremity ulcers, including diabetic foot (DFU) and venous leg ulcers (VLU). The primary endpoint is PAR in 4 weeks, with a goal healing rate of 40% in 4 weeks. There is a large body of evidence that supports this rate of healing for DFUs and VLUs [10], and the FDA-sponsored Wound Care Collaborative Community (WCCC) has recommended it as a surrogate endpoint [11].

In addition, an important endpoint in antiseptic clinical trials is a reduction in bacteria. The use of point-of-care fluorescence imaging has simplified this process. Fluorescence imaging will be obtained at every visit and the reduction in bacterial bioburden will be compared between ulcers treated with NSS-HG and AMC-AMG.

Additional secondary endpoints common to most wound-healing clinical trials will be the difference in pain scores and adverse events between subjects treated with NSS-HG and AMC-AMG.

Exploratory endpoints are encouraged if they do not interfere with the primary or secondary endpoints. They contribute to the body of knowledge on chronic wounds and can improve the conduct of future trials. This study will examine host protease levels (matrixmetaloproteases 8 and 9 and neutrophil elastase) using a point-of-care lateral flow test (WOUNDCHEK PROTEASE TEST, WoundChek, Gargrave, UK). In clinical trials, the diagnostic accurately identified wounds with high levels of inflammation. In wounds with a positive test for elevated protease activity (EPA) only 10% were healed at 12 weeks [12].

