### 2.3. Diagnosis

One of the challenges in conducting clinical trials in wound healing is ensuring that the wound type under study has been appropriately diagnosed. The clinical trial described here examines two ulcer types: diabetic foot (DFU) and venous leg ulcerations (VLU). The diagnosis of these two wounds is primarily clinical. DFUs occur on the plantar aspect of the foot in diabetic patients with sensory neuropathy. An objective assessment of vascular status using the ankle brachial index (ABI), the toe brachial index (TBI), or another screening test will rule out patients with significant ischemia. Venous leg ulcers develop on the medial or lateral gaiter regions of the lower extremities. Most clinical trials enroll VLU patients based on clinical signs and symptoms: lower extremity edema, hyperpigmentation of the skin, loss of hair, atrophy blanch, thickening of the nails, and lip dermatosclerosis. The venous ulcer is shallow with an irregular border. For ulcers that exhibit these signs, the diagnosis is straightforward. For ulcers suspected to be VLUs but that do not have the characteristic appearance, the investigator should consider biopsy to rule out vasculitis, cancer, or other pathology. The investigator may also wish to obtain a venous duplex scan to demonstrate venous insufficiency. In the past, VLU clinical trials mandated venous duplex procedures; however, this adds considerable cost to the trial without adding significant benefit.

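### The first exclusion criterion, read as written, makes every venous leg ulcer ineligible, although venous leg ulcers are named in the primary objective and the inclusion criteria

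*Protocol article*

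**What the plan says.** Several sections of the protocol article put VLUs in the trial.

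- Section 2.1 sets the primary objective "in chronic lower extremity ulcers, including diabetic foot (DFU) and venous leg ulcers (VLU").
- Section 2.3 states: "The clinical trial described here examines two ulcer types: diabetic foot (DFU) and venous leg ulcerations (VLU"). It places DFUs on the sole of the foot in diabetic patients with sensory neuropathy. For suspected VLUs it offers a duplex scan as a way to show venous insufficiency.
- The inclusion list in Section 2.6 requires "The presence of a DFU extending through the dermis or subcutaneous tissue or the presence of a full-thickness VLU", and sets "a VLU size between 2.0 cm^2^ and 20.0 cm^2^ at first treatment visit".
- Section 2.5 describes the standard of care for VLUs, and Section 2.7 provides multilayer compression for them at treatment visits.

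The exclusion list in the same Section 2.6 opens: "If any of the following exclusion criteria are met, patients will be excluded from participating in the study". Its first item is "Study ulcer(s) deemed by the investigator to be caused by a medical condition other than diabetes". A later item excludes a "Subject who cannot adhere to strict offloading according to protocol standards", in the investigator's opinion. Section 2.7 marks the fitting of an off-loading walker as applying to DFUs.

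**The concern.** The inclusion and exclusion lists cannot both be followed for a VLU. One list admits the ulcer because it is venous, and the other rejects it because its cause is not diabetes. Eligibility decides whom the trial result describes, so this affects more than wording.

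Up to five sites (Section 2) would each have to choose between obeying a listed exclusion and disregarding it. Obeying it leaves one of the two named ulcer types unstudied. Disregarding it means enrolling patients against a written criterion. A mixture of the two makes the proportion of VLUs in the trial a product of local interpretation.

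**Working it through.** No arithmetic applies to the contradiction itself. The check sets the eligibility rules side by side and runs each kind of ulcer through them.

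**Rules used (Section 2.6)**

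1. Inclusion by type: a DFU or a full-thickness VLU, each with its own size range.
2. First exclusion: the investigator judges the ulcer to be caused by a medical condition other than diabetes.
3. Operation of the list: any single exclusion is sufficient.

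**Cause by ulcer type (Section 2.3):** a DFU is tied to diabetes with neuropathy, and a VLU to venous insufficiency.

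| Index ulcer | Meets inclusion by type? | Meets the first exclusion? | Result as written |
|---|---|---|---|
| DFU | Yes | No | Eligible on this point |
| VLU, patient without diabetes | Yes | Yes; diabetes cannot be the cause | Excluded |
| VLU, patient with diabetes | Yes | Yes; the ulcer is attributed to venous disease | Excluded |

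The third row escapes only if the investigator attributes the ulcer to diabetes, which is at odds with diagnosing it as a VLU. The criterion turns on the cause of the ulcer, so having diabetes as a comorbidity does not rescue the patient.

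**Search for an exemption.** Sections 2.1, 2.3, 2.5, 2.6 and 2.7 contain no wording that limits the first exclusion to DFU candidates or exempts VLUs.

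**Size.** The number affected would be the VLU share multiplied by the planned maximum of 60 subjects. The article gives no VLU share, so the product cannot be evaluated. The figure of 30 per group in Section 2.8 uses no ulcer split and does not change as a direct result of this point.

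**Effect on the comparison of arms.** Section 2.7 moves patients who meet the eligibility requirements on to the first treatment visit, where they are randomised. Randomisation is 1:1, in blocks, stratified by site. A site's reading of the exclusion therefore acts before allocation and applies equally to both of its arms. Differences in ulcer mix between sites change who is studied, but do not by themselves create a systematic difference between arms.

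**The case against.** The strongest reply is that the intent is plain. The objective, the diagnosis section, the inclusion criteria, the size range and the compression procedure all include VLUs. A sensible site would read the first exclusion as meant for DFU candidates, so a trial with no VLUs is unlikely. The article also condenses a fuller protocol, and sites may be working from better wording. This stands as a limit on how confidently site behaviour can be predicted. It does not remove the contradiction: the criterion is stated, not omitted, and clear intent is a reason to correct the text. Nor does the investigator's discretion help, because it covers only the cause of the ulcer.

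A reader might also infer more than the documents support:

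- **A biased treatment comparison.** Stratified 1:1 allocation after eligibility is settled argues against this.
- **Loss of a VLU stratum from a per-protocol analysis.** The article defines no per-protocol set and stratifies by site only.
- **A count of affected subjects.** Taking one third to one half of 60 would give 20 to 30, but nothing in the article supports those shares.
- **A second contradiction in the off-loading exclusion.** That item refers to protocol standards, and the protocol assigns off-loading to DFUs, so it partly limits itself. It needs clarifying, no more.
- **A list carried over from a DFU-only protocol.** This is possible, but the osteomyelitis item covers the leg as well as the foot, and the origin of the text cannot be established from the article.

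**Conclusion.** The concern holds as an internal contradiction in a stated rule. As written, no ulcer attributed to venous disease is eligible, and the trial could not address the VLU part of its primary objective. If the clause is ignored, each VLU enrolled breaches a listed exclusion. If it is read unevenly, the ulcer mix and the population to which the result applies vary with site interpretation.

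The size can be stated only for the class: all VLUs are affected, in a number the document does not allow anyone to derive. The conclusion rests on one premise, that a diagnosed VLU is attributed to venous disease and not to diabetes, which is how Section 2.3 presents it. It does not extend to bias between arms or to the sample size.

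**What to change.** Reconcile the first exclusion in Section 2.6 with Sections 2.1 and 2.3 and with the inclusion list. Suggested wording: exclude a study ulcer that the investigator judges to be caused by a condition other than the one that defines its type, namely diabetes for a DFU and venous disease for a VLU. Issue the same wording to all sites.

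As a minor clarification, state that the off-loading adherence exclusion applies to DFU subjects, in line with Section 2.7.

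The cost is a one-sentence eligibility amendment, a short clarification and a memo to sites. No extra patients are needed, and neither the analysis nor the sample size changes.
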